This will be a controlled, randomized, double-masked trial. The Test group will wear the myopia control spectacle lens and the Control group will wear the single vision spectacle lens.

Primary outcome measure:

The mean change from baseline in objective cycloplegic refractive error in each of the groups (Test and Control)

Secondary outcome measure:

The mean change from baseline in axial length in each of the groups (Test and Control)

| Trial Product |
| --- |

Test lenses: Myopia control design spectacle lens, material: 1.6 High-Index plastic.

Control lenses: Single Vision design spectacle lens, material: 1.6 High-Index plastic.

Both test and control lenses will be designed and manufacture by Shamir Optical Industries Ltd.

Both test and control lenses will be mounted on regular frames.

Test lens

The test lens is manufactured in a standard FreeForm technology (exactly like a standard progressive addition lens which is similar in terms of the graduall power profile induced in both lens). It does not demand any special manufacturing processes.

The test lens should be worn exactly like a standard spectacle lens and it should be worn through all day hours. The fitting of the test lens is done exactly like the fitting of the control lens, according to the manufacturer instructions.

Product Labeling and Accountability

The clinical trial coordinator, who is in charge of the randomization procedures, will be also in charge of labeling the test spectacles per each patient prior to sending the spectacles to the site. The investigator will hold a dispensing log in which there will be a documentation of the product:

- on receival from the manufacturer
- on dispensing to the patient
- on receiving back from the patient if applicable

| Enrollment |
| --- |

**136** participants will be enrolled in this trial (including an estimated dropout rate of ~5%), 68 participants will be randomly allocated to the Test group and 68 participants will be randomly allocated to the Control group.

Sample size calculation

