- Previously been treated with any myopia control treatments (Orthokeratology, myopia control spectacle/contact lenses, multifocal lenses, bifocal lenses, atropine)

| Trial Plan |
| --- |

Screening visit **(VISIT 1)**

- Enrollment criteria verification
- Signing informed consent
- Baseline documentation of medical history, parental and siblings myopia, indoor and outdoor activities profile and socioeconomic profile
- Lensmeter measurements of patient's spectacles
- Performing baseline measurements including best corrected VA, objective & subjective refraction under cycloplegia, PR under cycloplegia*, slit lamp examination, functional tests: cover test, titmus test, worth four dot test, axial length** and pupil size measurements
- Frame selection and frame measurements
- Lens order completion and sending to Shamir Optical Industries for manufacturing

Randomization Procedures (following VISIT 1)

Randomization procedures should be performed by the trial coordinator following visit 1. The patient will then be allocated to the test or control group.

Manufacturing Procedures (following VISIT 1)

The manufacturing technician will take care of the manufacturing processes according to the lens type (ib test or control) and the mounting on the frame. The test spectacles will then be sent to the site for delivery.

Delivery visit **(VISIT 2)** performed ~10 days after screening visit

- Trial spectacles delivery
- Subjective questionnaire while wearing the trial spectacles
- Best corrected far and near VA (with the trial spectacles)
- Confrontation visual field test with the trial spectacles
- Giving instructions about wearing the trial spectacles
- Documenting adverse events if relevant

Follow-up visit performed 6 months (±1 week) after the previous visit **(VISITS 3,4,5,6)**

- Documentation of any change medical history since last visit
- Subjective questionnaire regarding the wearing period with the trial spectacles (feedback performing follow-up measurements including best corrected far and near VA, objective & subjective refraction under cycloplegia, PR under cycloplegia*, slit lamp examination, functional tests: cover test, titmus test, worth four dot test, axial length and pupil size measurements

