The optical design of the test lens, with the gradual positive peripheral power, induce a certain amount of aberrations in the peripheral areas of the lens. These aberrations were designed such that a good level of compliance will be achieved so that the children will be able to wear the lens.

Adverse events are unlikely to occur, yet it should be mentioned that a child should not wear this lens in case of one/more of the following exist:

- Feeling significant amount of discomfort while wearing the lens such that the safety of the child might be at risk.
- Vestibular disorders

The children participating in the trial will be free to contact the investigator at any time during the wearing period in order to report any unexpected events that might occur. The investigator will decide based on the report whether the child should be excluded from continuing the trial.

Furthermore, it should be noted that a parallel clinical trial is being conducted these days in AIER hospital in China, managed and supervised by Brien Holden Vision Institution (Australia). The trial is similar to our trial, with the same trial product, on a group of 140 children with the same enrollment criteria, including similar trial procedures and trial plan. The trial started at November 2020, and as for now most of the children has worn the test spectacles for a few months with no adverse events reported.

| Data Management |
| --- |

Database

An electronic data base will be held and maintained, into which all the source data will be electronically transferred from the measuring devices, or if not possible, will be typed in and source data (printouts or location of data) will be kept in the patient's file. At any case, all source data (printouts or location of data) should be kept in the patient's file.

The electronic data base will be backed up on a daily basis

Access to data:

The investigator will be able to allow access to data to the Sponsor (without identification data) as per request.

The investigator will be able to allow access to data to the Monitoring staff according to the monitoring plan that will be defined.

| Data Analysis |
| --- |

Data analysis will be performed by a third party. The trial raw data (without the identification data) will be transferred to the third party following the completion of each follow up visit. The third party will then perform the data analysis and produce a report to the sponsor.

Outcome measures analysis:

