The effect of the test lens compared to the control lens will be evaluated using the outcome measures mentioned above.

Both the primary outcome measure (the mean change from baseline in objective cycloplegic refractive error) and the secondary outcome measure (the mean change from baseline in axial length) will be calculated per each of the follow up periods mentioned above (6, 12, 18 and 24 months).

The objective cycloplegic refractive error will be calculated in Sphere Equivalent units which is: SPH + CYL /2 wherein the SPH and CYL values will be taken from the objective cycloplegic refraction measurement.

The mean change (and its standard deviation) of each of those parameters per each follow up visit will be calculated as the mean parameter at the follow up visit minus the mean parameter at the baseline visit.

The effect of the lens in terms of progression in those outcome measures will be analyzed using t-test (if data normality exists) and also by using linear mixed models which should be adjusted for age, gender, objective refraction (sphere equivalent), axial length, age of myopia onset, parental myopia, daily time wearing spectacles and time spend outdoors.

The effect we expect to have in the test group is a decrease in one/more of those parameters mean change from baseline (decrease in progression from baseline) compared to the control group. Any such finding that will include a p-value≤0.05 will be defined as statistically significant.

This analysis will be performed for all the sample as a whole and also for sub groups of age (younger and older children as mentioned above).

Differences of baseline parameters between the test and control group

The distribution of the following baseline parameters will be calculated per each of the groups, test and control:

- Objective cycloplegic refractive error (Sphere equivalent)
- Axial length
- Age
- Gender
- daily time spent outdoors
- Parental myopia

Should any significant difference be found between the two groups in any of those parameters, an adjustment should be made in the analysis regarding this parameter.

| References |
| --- |

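### The efficacy mixed model adjusts for daily spectacle wear, most likely a post-randomisation variable that the lens could change, so its lens coefficient need not be the effect of assigning the lens

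*Protocol*

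**What the plan says.** Under Data Analysis, Outcome measures analysis, the lens effect on the primary outcome (change in cycloplegic refraction) and the secondary outcome (change in axial length) is to be "analyzed using t-test (if data normality exists) and also by using linear mixed models which should be adjusted for age". The covariate list continues through gender, refraction and axial length to "age of myopia onset, parental myopia, daily time wearing spectacles and time spend outdoors". Wear time is given no measurement time, and the adjusted model is not labelled a sensitivity or compliance analysis. The section then counts as significant any reduction in progression, on one or more of the outcomes, with p at or below 0.05. It does not say which of the two analyses must show it.

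Other sections bear on when wear is recorded and what it means:

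- Trial Plan, Visit 1: "Baseline documentation of medical history, parental and siblings myopia, indoor and outdoor activities profile and socioeconomic profile". Wear time is not mentioned.
- Trial Plan, after Visit 1: "Randomization procedures should be performed by the trial coordinator following visit 1". The spectacles are made and delivered after that.
- Trial Plan, Visits 3 to 6: "Subjective questionnaire regarding the wearing period with the trial spectacles".
- Trial Product, on the test lens: "it should be worn through all day hours".
- Risk Evaluation/Adverse Events: the test lens's optics "induce a certain amount of aberrations in the peripheral areas of the lens", and "These aberrations were designed such that a good level of compliance will be achieved". Significant discomfort that might put safety at risk is given as a reason for a child not to wear it.

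**The concern.** The trial's stated purpose is to compare the clinical effect of the test lens with that of a single vision lens. Randomisation supports that comparison when the arms are compared as assigned, or after adjustment for variables fixed before assignment.

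Hours of wear of the trial spectacles are not fixed before assignment. They are part of how the lens works or fails: a lens that is poorly tolerated is worn less and gives less benefit. A model that holds wear equal across arms asks what the lens would do if both groups wore it for the same time, and removes any gain or loss that comes through wear.

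There is a second problem. If some unmeasured feature of a child influences both wear and progression, conditioning on a wear variable that the lens has shifted creates a non-causal link between lens and progression. Neither problem shrinks as the sample grows.

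**Working it through.** **1. What the plan's effect size refers to.** The Sample size calculation gives a difference of 0.18 D per year (30% of 0.6 D), SD 0.35 D and 60 per group. Power and sidedness are not stated. Two-sided 0.05 with 80% power reproduces the figure: n = 2 × (1.96 + 0.84)² × 0.35² / 0.18² ≈ 59.3, rounded up to 60 (power 80.4%). Then 120 × 1.05 = 126, and 126 + 10 = 136, the stated total. This is an unadjusted comparison of two means, so the planned 0.18 D is a difference between arms as assigned.

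**2. When wear time is measured.** Compare the model's covariates with the baseline parameters listed later in Data Analysis (refraction, axial length, age, gender, outdoor time, parental myopia). Two covariates are not in that list: age of myopia onset and wear time. Onset age necessarily precedes randomisation. Wear time does not, and Visit 1 does not record it. The questionnaire at delivery comes after randomisation and before any wearing period. The only stated inquiry about a wearing period is at Visits 3 to 6. Post-randomisation measurement is therefore an inference, but much the likelier reading.

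**3. What adjustment does.** Take the outcome as change in refraction, with a positive lens effect meaning less progression. Let d be the difference in mean wear, test minus control (h/day), and b the pooled within-arm slope of the outcome on wear (D per h/day). For a linear model with this one covariate:

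adjusted effect = effect of assignment − b × d

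The documents give neither b nor d. The values below are assumptions chosen only to show the behaviour, with an effect of assignment of 0.18 D:

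| d (h/day) | b = −0.05 | b = 0 | b = +0.05 |
| --- | --- | --- | --- |
| 0 | 0.18 | 0.18 | 0.18 |
| −0.5 | 0.155 | 0.18 | 0.205 |
| −1 | 0.13 | 0.18 | 0.23 |
| −2 | 0.08 | 0.18 | 0.28 |

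For example, 0.18 − (0.05 × −1) = 0.23. If the test lens is worn more rather than less, the signs reverse.

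**4. Check by simulation** (200,000 children, true effect of assignment 0.18 D):

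- d = −1, b = 0.05, no shared cause: unadjusted 0.182 D, adjusted 0.232 D.
- d = −1, no causal effect of wear, but an unmeasured cause shared with progression (wear SD 1.5 h, correlation 0.5 with that cause, 0.1 D per SD of it): unadjusted 0.182 D, adjusted 0.216 D. The induced slope is 0.1 × 0.5 / 1.5 = 0.033 D per hour, so the expected result is 0.182 + 0.033 = 0.215 D.
- d = 0: adjusted and unadjusted agree at about 0.18 D under every setting tried.

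The shift thus needs two things: the lens changes wear, and wear is associated with progression, whether causally or through common causes.

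**The case against.** **Timing is not stated.** Absence from the baseline list does not prove late measurement, since onset age is absent too. Visit 1 includes lensmeter readings of the child's own spectacles and an activity profile, so habitual wear could have been asked about there, and the follow-up questionnaire item does not mention hours. If habitual pre-trial wear was meant, the point falls. This stands as a limit on certainty, but nothing in the text supports that reading.

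**The t-test is unadjusted.** It compares the arms as randomised, subject to dropout, and matches the sample size calculation. That is correct and limits the damage. It does not remove it: the t-test is conditional on normality, no analysis is named as deciding, and a p-value at or below 0.05 counts without reference to the method. The mixed model could carry the claim alone.

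**A reader might infer that the protocol predicts less wear in the test arm.** It does not. The risk section says compliance was designed for, the background table compares compliance with competing myopia-control lenses rather than with the single vision control, and the trial is described as double-masked. The documents support only that the lens could affect wear.

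**A reader might also put a figure on the loss as a share of the planned effect.** The inputs would be invented. Moreover, the background section holds that single vision lenses accelerate progression while defocus lenses reduce or reverse the peripheral defocus said to drive it. On that theory the wear slopes could have opposite signs in the two arms, and a pooled slope would partly cancel.

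**A reader might extend the point to refraction, axial length and outdoor time,** because the model list does not attach the word baseline to them. The same section names all three as baseline parameters, so this is a matter of clearer wording and not a defect.

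**Conclusion.** The concern holds for one covariate in one of the two planned analyses. As written, the mixed model conditions on a variable that is most likely measured after randomisation and that lens tolerability could change. Its lens coefficient then equals the effect of assigning the lens only if the lens leaves wear unchanged or wear is unrelated to progression.

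The distortion cannot be sized or signed from the documents; the 0.08 to 0.28 D range includes no shift and rests wholly on assumed values. The conclusion depends on the inferred timing of measurement. The sample size and the unadjusted t-test are not called into question. The point still deserves correction because the protocol lets the mixed model support the efficacy claim by itself.

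**What to change.** In Outcome measures analysis, delete daily wear time from the covariates of the efficacy mixed model and state that the remaining covariates are pre-randomisation variables entered at their Visit 1 values. Report wear time by arm at each follow-up visit. If an analysis using wear is wanted, specify it separately as a supplementary compliance analysis that does not decide efficacy. If habitual wear before randomisation was what was meant, say so and add it to the Visit 1 data; it may then stay in the model.

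The cost is a sentence or two of protocol or SAP text. Wear data can still be collected, and the sample size does not change. Because data go to the third-party analyst after each follow-up visit, the change should be made before results are first compared by arm.

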The annual myopia progression rate (in objective refraction) in children in Israel is estimated as 0.6D. The effect estimated is 30% which is a change of 0.18D between the annual myopia progression rate at the test group and the control group. Taking into account a standard deviation of the progression rate of 0.35D (as reported in the scientific literature in western countries), the sample size of each group (test and control) should include 60 children.

Taking into account a drop out rate of 5% and also a certain amount of drop outs during the trial due to high annual myopia progression (as mentioned in the section about terminating the participation in the trial) for which we added 10 more patients, the overall calculated sample size is 136.

Distribution of ages within the sample:

The age range for inclusion in the trial is 6 to 12 years old and the children will be enrolled into two aged groups: young children and older childern. In order to create an equal amount of children within each age group the enrollment will be as follows:

- Young Children: Age ≥6, <9.5: 68 patients
- Older Children: Age ≥9.5, <13: 68 patients

Randomization

Randomization function should be applied separately per each of the two age groups, so that eventually each group will contain an equal number of Test lens wearers and the Control lens wearers.

Randomization function will be applied per each age group by the clinical trial coordinator who will keep the randomization list in a confidential file and will not disclose it to other trial staff members (except for the manufacturing technician at Shamir Optical Industries) until the trial close up unless required in specific cases of trial withdrawals by the investigator.

Inclusion Criteria

- Informed consent form signed and fully comprehended by the parent/legal representative of the child
- Age from 6 to 12 years old
- Both male and female
- Spherical Equivalent refractive error (cycloplegic objective) of -0.50D to -5.00D
- Astigmatism not higher than -1.50D
- Corrected Visual Acuity of not less than 6/7.5 or 20/25
- Willing to wear the trial spectacles for the defined period according the protocol plan

Exclusion Criteria

- Current participation in another clinical trial
- Any general health or ocular health pathology that could affect the treatment
- Allergy or intolerance to cycloplegic eye drops (*name should be stated here*)
- Strabismus
- Amblyopia
- History of ocular injury or ocular surgery

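### The significance rule accepts p≤0.05 on either outcome, at any of four visits, in all children or either age group, so a lens with no effect has roughly a 15–35% chance of a nominally significant favourable result

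*Protocol*

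**What the plan says.** Trial Design names one primary outcome, "The mean change from baseline in objective cycloplegic refractive error in each of the groups (Test and Control", and one secondary, "The mean change from baseline in axial length in each of the groups (Test and Control".

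The Data Analysis section (Outcome measures analysis) repeats those labels and then sets out the testing:

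- **Visits.** Both outcomes "will be calculated per each of the follow up periods mentioned above (6, 12, 18 and 24 months".
- **Methods.** A t-test, provided the data are normal, and in addition linear mixed models adjusted for a list of covariates.
- **Populations.** "This analysis will be performed for all the sample as a whole and also for sub groups of age", meaning the younger and the older children.
- **What is looked for.** "The effect we expect to have in the test group is a decrease in one/more of those parameters mean change from baseline", relative to control.
- **Threshold.** "Any such finding that will include a p-value≤0.05 will be defined as statistically significant".

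No other criterion for judging the lens is given. The same section sends the data to a third-party analyst after each follow-up visit, who then reports to the sponsor.

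The sample size calculation rests on a single quantity: "The effect estimated is 30% which is a change of 0.18D between the annual myopia progression rate" of the two groups, with an SD of 0.35 D and 60 children per group.

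**The concern.** The primary label protects the error rate only if the decision rests on the primary outcome. Here the expected effect is "a decrease in one/more of those parameters mean change from baseline", and any such result at 0.05 carries the same status, whichever outcome, visit, age group or method produced it. A favourable axial-length result at 6 months in the older children by t-test would qualify as fully as refraction at 12 months in everyone. The sample size, by contrast, assumes one test.

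Two things are at stake. The 5% threshold no longer describes the chance of a false-positive finding from the trial. Separate tests in each age group will also often suggest that the lens works at one age only when the true effect is the same in both.

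**Working it through.** **1. The protocol's own figure.** Inputs from the sample size calculation: difference 0.18 D (30% of 0.6 D), SD 0.35 D. Power and sidedness are not stated. At two-sided 0.05 and 80% power:

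n per group = 2 × [(1.960 + 0.842) × 0.35 / 0.18]² = 59.4, rounded up to 60.

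This reproduces the stated 60. One-sided 0.05 at 80% power would give 47. The total also reproduces: 120 × 1.05 + 10 = 136. The design is therefore consistent with one two-sided 5% test of annual refraction change.

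**2. Number of tests.** 2 outcomes × 4 visits × 3 populations = 24. With the mixed model also tested at every visit, 24 × 2 = 48. The 48 is a maximum.

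**3. Chance of a favourable finding when the lens does nothing.** Only results favouring the test lens count, because the rule refers to a decrease in progression. One pre-specified two-sided test gives 0.05 / 2 = 2.5%. If the 24 tests were independent, the chance would be 1 − 0.975²⁴ = 46%. They are strongly correlated, so that is only an upper reference and simulation is needed.

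The protocol gives no correlations, so all of the following are assumptions:

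- First set (8,000–10,000 replicates per setting): 30–34 children per arm per age group; correlation between outcomes 0.5–0.9; visits correlated through accumulating change, autoregressively (0.7 or 0.9) or exchangeably (0.7–0.9); covariates explaining 0–30% of variance.
- Second set (3,000–4,000 replicates per setting): 34 per arm per age group; a child-specific slope plus noise giving a 12-month SD of 0.35 D; correlation between outcomes 0.6–0.9; covariates explaining about 25% of the slope.

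Chance of at least one two-sided p≤0.05 favouring the lens:

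| Tests counted | Chance |
| --- | --- |
| One pre-specified test (check) | 2.2–2.7% |
| Two outcomes, four visits, whole sample only, t-test | 6–12% |
| All 24, t-test only | 13–24% |
| 24 t-tests plus one longitudinal test per outcome and population | 16–29% |
| All 48, adjusted test at each visit (first set) | 18–33% |
| All 48, adjusted test at each visit (second set) | 20–37% |

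If the 0.05 were one-sided, the first set gives 27–36% by t-test alone and 36–44% with both methods.

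**4. Age-group tests.** 60 evaluable per group means 60 / 2 = 30 per arm in each age group; 68 enrolled per group means 68 / 2 = 34. The power of a two-sample t-test follows from the noncentrality (0.18 / 0.35) × √(n/2):

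- n = 30: noncentrality 1.99, power 50%.
- n = 34: noncentrality 2.12, power 55%.

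With the same true effect in both age groups, the chance that exactly one is significant is 2 × power × (1 − power). This is 2 × 0.50 × 0.50 = 50%, or 2 × 0.55 × 0.45 = 49.5%.

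**The case against.** The strongest reply is that the protocol does name a primary outcome, that the disputed sentence opens as a statement of expectation, and that it defines statistical significance rather than trial success. A statistical analysis plan, not shown here, may name the deciding visit, the order of testing and an interaction test. Their absence from a protocol is not in itself a fault. That stands. What remains is that the protocol does state a rule, that it offers no other criterion, and that any hierarchy in an analysis plan would have to contradict it.

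Three stronger readings are tempting, and the document does not support them:

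- A reader might infer that an ineffective lens has a 1-in-4 to 1-in-3 chance of being declared effective. The protocol never says when the lens would be declared effective, and those odds are the upper part of a range that depends on unstated correlations.
- A reader might take 48 tests as the plan. The t-test is conditional on normality, and a linear mixed model is commonly one longitudinal fit per outcome. Longitudinal tests alone, for both outcomes in all three populations, gave 8–10% in the second set of assumptions.
- A reader might quote the chance of significance in either direction, which reaches 42–62% for 48 tests in the second set. The rule counts only results favouring the test lens, so that figure does not describe it.

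**Conclusion.** The point holds in this form. The one-or-more wording, joined to the any-finding threshold, undoes the protection of the primary label. It raises the chance of a nominally significant favourable result under no effect to roughly 15–35%, against 2.5% for one pre-specified two-sided test. The figure assumes two-sided p-values, the correlations listed above, and either one longitudinal mixed-model test per outcome and population or an adjusted test at each visit. With t-tests alone and very high correlations it falls to about 13%, still about five times 2.5%.

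The age-group result rests on the protocol's own 0.18 D and 0.35 D and on 30–34 children per arm: about 50–55% power in each age group, and about an even chance that exactly one is significant when the effect is the same in both. Because the rule governs the trial's main conclusion, it should be corrected before unmasked results are seen.

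**What to change.** Delete the one-or-more expectation and the any-finding threshold as the basis for judging the lens. Before any unmasked results are seen, name one primary test:

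- the between-group difference in change from baseline in cycloplegic spherical equivalent;
- all randomised children;
- one visit and one method;
- baseline covariates only, since daily spectacle-wearing time, now in the covariate list, may itself be affected by the lens;
- two-sided 0.05.

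The stated sample size supports 12 months. If 24 months is chosen, restate the sample-size basis in 24-month terms, with its SD given as an assumption because the protocol supplies none. Whether 136 children would then suffice cannot be judged from the document.

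Test axial length only if the primary test is significant. Report the other visits and methods as supportive, without significance claims. For age, test the treatment-by-age-group interaction and give an estimate with a confidence interval for each age group.

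With the 12-month choice, the cost is wording only, with no added children or visits. The downside is that the sponsor gives up claims based on whichever outcome, visit, method or age group looks best. A fixed sequence is one of several valid ways to control the error rate; what matters is that one is fixed in advance.

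### Two analyses stand side by side with neither named as the main one, and a baseline-significance trigger for adjustment is redundant for the mixed model and can only alter the t-test route by chance

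*Protocol*

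**What the plan says.** All of this is in the protocol; no SAP was at hand.

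- **Two methods.** Under Data Analysis, Outcome measures analysis, the lens effect is to be analysed "using t-test (if data normality exists) and also by using linear mixed models". The models are those "which should be adjusted for age, gender, objective refraction (sphere equivalent), axial length, age of myopia onset, parental myopia, daily time wearing spectacles" and time outdoors, which makes eight covariates. No method is called primary, and nothing is given to replace the t-test if normality fails.
- **Success rule.** "Any such finding that will include a p-value≤0.05 will be defined as statistically significant". The sentence does not say which of the two analyses must supply the p-value.
- **Baseline screen.** Under the heading on baseline differences between the groups, "The distribution of the following baseline parameters will be calculated per each of the groups, test and control". Six are listed: cycloplegic refraction, axial length, age, gender, time outdoors and parental myopia. Then comes the trigger: "Should any significant difference be found between the two groups in any of those parameters, an adjustment should be made in the analysis". Neither the significance level of these tests nor the analysis to be adjusted is stated.
- **Randomisation.** Under Enrollment, Randomization: "Randomization function should be applied separately per each of the two age groups". Age group is the only stratification factor.

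**The concern.** Under sound randomisation a significant baseline difference is a chance event. Its p-value does not show whether the variable predicts progression, and prediction is what makes adjustment worthwhile. A strong predictor deserves adjustment even when it happens to be balanced; a weak one gains nothing from it even when it is not.

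The trigger also fits badly with the text before it. Every variable it screens is already in the mixed model, so it either does nothing, turns the t-test into some other analysis, or invites a further model once baseline data have been seen. Two competent analysts could follow the text and report different estimates.

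At stake are three things: a free choice between two analyses under a rule that credits any p≤0.05; power given up if the t-test is the one that leads; and a t-test whose standard error takes no account of the age-stratified allocation.

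**Working it through.** **1. The plan's own sample size.** Inputs from Enrollment, Sample size calculation: difference 0.18 D, SD 0.35 D, 60 per group. Power and sidedness are not stated; 80% and two-sided 5% are assumed.

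n = 2 × (1.960 + 0.842)² × (0.35/0.18)² = 2 × 7.85 × 3.78 ≈ 59.4, so 60 per group. The figure reproduces as an unadjusted two-sample comparison. Exact t-test power at 60 per arm is 79.8%.

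**2. Does the trigger reach the mixed model?** Screened: refraction, axial length, age, gender, time outdoors, parental myopia. In the model: those six plus age at myopia onset and daily wear time. All six are already there, so the trigger cannot change the model's covariate list.

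**3. How often does it fire by chance?** With six independent tests at an assumed 0.05: 1 − 0.95⁶ = 26.5%. Correlation between refraction and axial length, and balance on age from stratification, both lower this. Simulation gives about 25% with correlated covariates and simple randomisation, and about 20-21% with age-stratified allocation. Range: 20-26%.

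**4. What does it do to error and power?** The simulation used 60 per arm, SD 0.35 and a true difference of 0 or 0.18 D. A single-visit analysis of covariance on the six screened variables stood in for the mixed model. None of the following is in the protocol: normal covariates; correlations of −0.7 (refraction with axial length), −0.3 (age with refraction) and 0.3 (age with axial length); and R², the share of outcome variance explained by the covariates. Results under simple randomisation:

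| R² | Power: t-test | Power: trigger rule | Power: pre-set adjustment | Type I: trigger rule | Type I: either analysis accepted |
|---|---|---|---|---|---|
| 0.1 | 79.9% | 79.6% | 81.7% | 4.9% | 6.8% |
| 0.2 | 79.7% | 80.0% | 85.7% | 4.9% | 7.4% |
| 0.3 | 79.3% | 80.2% | 90.6% | 4.2% | 7.4% |
| 0.4 | 79.9% | 80.8% | 93.9% | 4.2% | 8.2% |

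Pre-set adjustment alone held type I error at 4.9-5.1%. Monte Carlo standard errors are about 0.15 points for error rates near 5% (√(0.05 × 0.95/20,000)) and about 0.45 points for power near 80% (√(0.8 × 0.2/8,000)).

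**5. The same check with age-stratified allocation.** Power is about 80-82% for the t-test or trigger rule and about 82-94% for pre-set adjustment. Accepting either analysis gives about 6-7% type I error. The unadjusted t-test becomes conservative, with true error of roughly 3-5% and lowest where the covariates, age among them, explain most. The design balances age, but the t-test's standard error still includes the between-age variation, so it is somewhat too wide.

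**6. Effect on the required number.** Replacing 0.35 by 0.35 × √(1 − R²) in step 1 multiplies 59.4 by 0.9, 0.8, 0.7 and 0.6, giving 54, 48, 42 and 36 per arm. The fix needs no extra children.

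**The case against.** The strongest reply is that the protocol already pre-sets an adjusted analysis. A reader might infer that the main estimate rests on chance baseline tests in place of a fixed adjusted model. The documents do not support that: the mixed model names eight covariates whatever the baseline table shows. This stands, and it confines the trigger to the t-test route.

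A reader might also infer that the trigger raises the false-positive rate. It does not; error under the rule stays at or below 5%. The 20-26% is how often it fires, not how often a wrong conclusion follows.

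Nor is the trial underpowered because of the t-test: 60 per arm was evidently sized for an unadjusted comparison, and ignoring the age strata costs precision without biasing the contrast. The power gain rests on an assumed R² and is already available in the mixed model. It would be lost only if the t-test led, which the protocol does not say. Baseline refraction is measured but not stratified, so the point about ignored strata concerns age alone.

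Finally, which analysis leads, and what follows if normality fails, are often settled in an SAP. That is fair for those two items. It does not rescue the trigger, the normality condition or the rule crediting any p≤0.05: these are written into the protocol, and an SAP that dropped them would depart from it.

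**Conclusion.** The point holds in limited form. The trigger is redundant for the mixed model and responds only to chance on the t-test route, firing in about 20-26% of sound trials if the baseline tests use 0.05. It leaves type I error uninflated and recovers almost no power.

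The larger weakness is that neither of two listed analyses is named as the main one. If p≤0.05 from either were taken as success, type I error would be about 6-8% for one endpoint at one visit. The protocol does not say outright that either suffices; its wording leaves that open.

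For 0.18 D with SD 0.35 D at 60 per arm, and covariates explaining an assumed 10-40% of variance, a pre-set adjusted model has about 82-94% power against about 80-82% for the t-test or trigger rule. The error and power ranges depend on the assumed R² and correlations and on a single-visit stand-in for the mixed model. The redundancy follows from the text alone.

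**What to change.** - Delete the trigger sentence and present the baseline table descriptively, without significance tests.
- Name the linear mixed model as the single main analysis. Include treatment, visit, treatment-by-visit, randomisation age group, baseline value of the outcome and the pre-set baseline covariates, whatever the observed imbalance.
- State the one visit at which the treatment contrast is the main result. The protocol reports at 6, 12, 18 and 24 months, while the sample size is framed in annual progression, so the two should be made to agree.
- Leave daily spectacle wear time out of this model where it is measured after randomisation, as appears to be the case, and use the baseline value of time outdoors.
- Keep the t-test as supportive only and remove the normality condition.
- Tie the p≤0.05 rule to the named main analysis.

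The cost is protocol wording, plus the ethics committee review that the protocol requires for any amendment. No extra children, visits or measurements are needed.
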